### Handling of missing data

Participant medical record/database review will minimise the presence of missing data for many outcomes. Descriptive statistics on the proportion of missing data by treatment arm will be provided for the outcomes and the covariates. If the level of missingness is below 5%, we will undertake a complete case analysis. If greater than 5% of the data are missing, we will evaluate if there are any differences between the baseline characteristics for participants with and without missing data. Using this evidence, we will determine whether a complete case analysis is valid. If covariate outcomes are missing and a complete case analysis is not valid, the primary analysis will be a joint Bayesian analysis of the missingness mechanism and outcome model. In general, we will not jointly model or impute missing outcomes. If outcomes are missing and a complete case analysis is not used, then we will report descriptive statistics for this outcome and the reasons that individuals were lost to follow-up.

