## Method/Design

### Design and setting

The BIPED study is a phase III study conducted in 12 sites across Canada, Australia and New Zealand. All participating hospitals are members of the Pediatric Emergency Research Canada (PERC) network [11] or the Paediatric Research in Emergency Departments International Collaboration (PREDICT) [12], both of which are affiliated with the Pediatric Emergency Research Networks (PERN). The BIPED study will define bronchiolitis as an episode of wheezing or crackles in an infant aged between 60 days and 12 months, alongside signs of an upper respiratory tract infection during the period deemed to be the season for RSV bronchiolitis. To reflect international clinical guidelines and practice, we have not restricted our definition of bronchiolitis to the first episode of wheezing or crackles and will enrol infants with second and subsequent episodes of bronchiolitis, with each infant only enrolled once into the study.

The active treatment in the BIPED study is two treatments of epinephrine (either via nebulisation (3 mg) or via metered dose inhaler and spacer (MDI-s) (625 mcg)) given 30 min apart in the ED and two doses of once daily oral dexamethasone (0.6 mg/kg per dose, up to a maximum of 10 mg), known as EpiDex. The first dose of dexamethasone will be given immediately before the first dose of epinephrine, and the second dose will be given 24 h later. The BIPED study will compare EpiDex to a placebo control (oral dexamethasone vehicle and nebulised normal saline or an inert placebo by MDI-s) by randomising participants in a 1:1 ratio. All study personnel, bedside clinicians, and participants/caregivers are blinded to the study group assignment. Participants will be followed up for 21 days following their ED enrolment visit, with the primary outcome collected at 7 days (168 h) post enrolment.

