### Sample size calculation

The sample size was determined using the average length criterion (ALC) [16], a Bayesian method for sample size determination. Using the ALC, we chose the smallest sample size for which the average length of the 95% high-density posterior credible interval for the difference in admission rates between placebo and EpiDex is below 9%. We determined the average length of the posterior credible interval across the prior-predictive distribution for the data [16]
. To determine the relevant prior distribution, we performed an expert elicitation for the probability of hospitalisation under placebo and EpiDex [17]. We simulated 1500 studies from the prior-predictive distribution and computed the posterior distribution for the absolute difference using 5000 simulations to estimate the average length of the 95% posterior credible intervals. Based on this simulation, the sample size of 410 participants per arm for the BIPED study was selected [17]. We allowed for a 5% loss to follow up, leading to a total target recruitment of 864 participants, 432 per arm.

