### Baseline characteristics

We will collect baseline information about the participants’ age, sex, weight, race, indigenous status and home environment, which includes the presence of smokers and attendance at daycare. We will also collect baseline clinical characteristics (respiratory distress assessment index (RDAI) [23], oxygen saturation, respiratory rate, heart rate, and temperature), the length of symptoms and treatments given prior to initial ED presentation, the medical history of the participant (such as breastfeeding, maternal smoking during pregnancy, prematurity, previous intubations, personal history of atopy [environmental allergy, food allergy and eczema, and previous significant/chronic illness], and previous episodes of wheezing/bronchiolitis) and family history of atopy (including asthma). Finally, if respiratory virus testing is available, the virus status will be reported.

Baseline characteristics will be compared across treatment groups and reported based on their data type. Specifically, categorical data will be summarised by numbers of participants within each category and percentages. If the continuous data are sufficiently normal, they will be summarised with the mean and standard deviation. Otherwise, the data will be summarised using the median and interquartile range. We will not undertake inferential statistics for baseline characteristics but will note the clinical importance of any imbalance.

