### Additional analyses

If the analyses are adjusted for missingness, we will also perform a complete case analysis by excluding subjects with missing values from the analysis to understand the sensitivity of the conclusions to missing data. We will also undertake a prior sensitivity analysis for the primary analysis using a minimally informative prior for the treatment effect.

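### Above 5% missing, complete-case validity is judged from a baseline comparison, with no criterion and not specified by arm, that does not reliably show whether the EpiDex–placebo contrast is biased

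*SAP article*

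**What the plan says.** The SAP article, Handling of missing data, sets a first step: "If the level of missingness is below 5%, we will undertake a complete case analysis". Above 5%, the team turns to baseline data: "we will evaluate if there are any differences between the baseline characteristics for participants with and without missing data". The next sentence makes that comparison the basis of the decision: "Using this evidence, we will determine whether a complete case analysis is valid". No test, cut-off or list of variables is given, and treatment arm is not mentioned in the comparison. The same section does report the proportion missing by arm, but as description and without a link to the decision.

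What follows depends on what is missing. If covariates are missing and complete case is judged invalid, a joint Bayesian model is fitted. Missing outcomes are in general neither modelled nor imputed; if complete case is not used for them, that outcome is reported descriptively.

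Additional analyses plans one missing-data sensitivity analysis, and it is conditional: "If the analyses are adjusted for missingness, we will also perform a complete case analysis". The other analysis listed there changes the prior.

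The list from which differences could arise is long. Baseline characteristics opens with "We will collect baseline information about the participants’ age, sex, weight, race, indigenous status and home environment" and goes on to clinical signs, history and family history. By my count it has about 21 to 25 items.

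**The concern.** Comparing infants with and without missing data at baseline asks whether missingness is related to baseline. Bias in EpiDex versus placebo is a different question: whether missingness is related to outcome in a way that differs between arms. Missingness that depends on a baseline factor equally in both arms leaves the contrast almost unbiased, yet shows up clearly in the comparison. Missingness among infants sent home that differs by arm biases the contrast, and the pooled comparison need show no more than it would if the loss were equal.

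The second pattern is the relevant one. An infant admitted at the enrolment visit already has the primary outcome, so loss falls mainly on infants sent home, and treatment may affect who is sent home.

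Both errors have consequences. A wrong flag removes the inferential analysis of the primary outcome. A wrong pass sends a biased estimate to the 99% superiority rule. Because outcomes are not modelled, the condition for the one missing-data sensitivity analysis is then not met.

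**Working it through.** **Inputs from the SAP article.** Sample size calculation: "the sample size of 410 participants per arm for the BIPED study was selected" and "We allowed for a 5% loss to follow up, leading to a total target recruitment of 864 participants, 432 per arm". Design and setting: allocation "by randomising participants in a 1:1 ratio". Statistical principles: hospitalisation probability 0.35, type 1 error 4.1%, target difference 8%.

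**The plan's own figure.** 410 / 0.95 = 431.6, rounded up to 432 per arm and 864 in total. This matches. Planned loss therefore sits at the 5% threshold. The plan gives no figure for how often the baseline comparison would show a difference.

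**Step 1. Chance of at least one difference when loss is fully random.** The criterion is not stated, so it must be assumed. For k independent variables tested at level α, P = 1 − (1 − α)^k.

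| k | α = 5% | α = 1% |
|---|---|---|
| 10 | 40% | 10% |
| 15 | 54% | 14% |
| 20 | 64% | 18% |
| 22 | 68% | 20% |

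At 5% the chance passes one half only from k = 14 (51%). With a standardised difference above 0.25 as the criterion and k = 20, it is 82% at 6% missing, 43% at 10% and 16% at 15%.

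**Step 2. Bias from unequal loss among infants sent home.** Assume no treatment effect, 35% admitted in each arm, loss only among the 65% not admitted, and none of the missing infants admitted. With loss proportion m, the observed admission proportion is 0.35 / (1 − 0.65m).

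- 15% v 3% (placebo v EpiDex): 0.35/0.9025 − 0.35/0.9805 = 0.388 − 0.357 = 3.1 points in favour of EpiDex.
- 12% v 6%: 0.35/0.922 − 0.35/0.961 = 0.380 − 0.364 = 1.5 points.
- 9% v 9%: 0.35/0.9415 in both arms, difference 0.

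Overall missingness is 0.65 × 9% = 5.9% in all three cases, just above the threshold.

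**Step 3. Does the comparison tell these cases apart?** Simulation: 432 per arm, 15 independent characteristics of which one is prognostic (log-odds 0.6 per SD), flag if any characteristic differs at the 5% level.

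| Loss among infants sent home, placebo v EpiDex | Bias, points | Flagged |
|---|---|---|
| 9% v 9% | 0 | 66% |
| 12% v 6% | 1.5 | 65% |
| 15% v 3% | 3.1 | 65% |

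The flag rate does not move because average loss among infants sent home is 9% each time, and pooling discards the split by arm. At a 1% test the flag rate falls below 30% and is again about the same in all three.

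With a cut-off calibrated to the plan's 4.1% type 1 error (z > 1.739), false superiority at 15% v 3% is 21% over all trials, and still about 21% among trials that pass the 5% check. Passing gives no protection here. About 35% of trials pass, so about 0.35 × 21% = 7% of all trials both pass and falsely declare superiority.

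**Step 4. Other mechanisms.** Second simulation: 864 infants, 22 variables (correlation 0.1), two prognostic (log-odds 0.4 per SD), 8% to 9% missing, no true effect. Bias is given as absolute size.

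| Missingness | Flagged, 5% test | Flagged, 1% test | Bias, points |
|---|---|---|---|
| Fully random | 66% | 19% | 0 |
| Depends on outcome, opposite by arm | 68% | 20% | 6.8 |
| Depends on outcome, one arm only | 70% | 24% | 4.1 |
| Depends on a baseline factor, opposite by arm | 64% | 20% | 1.5 |
| Depends on a baseline factor, one arm only | 98% | 86% | 0.7 |
| Depends on a baseline factor, same in both arms | 100% | 100% | about 0 |

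The largest bias, near the 8-point target difference, is flagged hardly more often than random loss. The case flagged every time has almost no bias.

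**The case against.** The strongest reply is that the section describes a judgement and not a test. It says differences will be evaluated and used as evidence; it does not say that one difference rejects complete case. For the comparison of treatment groups, Baseline characteristics even rules out inferential statistics. This stands. A reader might infer that the rule fires more often than not when nothing is wrong. The document does not support that: it needs an assumed 5% test on at least 14 independent variables, a 1% test on 15 to 22 variables gives 14% to 20%, and a descriptive judgement has no firing rate.

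Nor can one say that the comparison flags equally often with and without bias. That holds for the unequal-loss cases in step 3 against equal loss. Fully random loss flagged 53% under the same settings, and step 4 ranges from 64% to 100% at the 5% test.

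The loss rates are also assumptions. Nothing in the document suggests a fivefold difference between arms in a double-blind trial, and the 3.1 points require that no missing infant was admitted. The 21% depends on the calibrated cut-off; at a nominal 1% cut-off (z > 2.326) it is 7.9%.

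Arm is not ignored altogether: missing proportions and withdrawals are reported by arm, so a 15% v 3% split would be visible. Visibility does not enter the stated decision, however, and leads to no analysis.

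Finally, follow-up calls and record review may keep missingness below 5%, and the step would then not be used. That is possible. But planned loss is at the threshold, and some sites rely on caregiver report for visits to non-study hospitals.

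**Conclusion.** The point stands as a weakness in the stated decision step that should be corrected. Above 5% missing, the only named evidence for complete-case validity is a comparison that does not separate biased from unbiased treatment contrasts, whether it is read as a test or as a judgement. It can lead to descriptive reporting of the primary outcome when loss is harmless. It can also let a biased complete-case result through with no missing-data sensitivity analysis behind it.

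The size is conditional. The illustrative bias is about 3 points under 15% v 3% loss among infants sent home with none of the missing infants admitted, and 1.5 points under 12% v 6%. The document gives only the 5% expected loss, so neither figure is a forecast for this trial.

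**What to change.** Two changes before data lock, which Trial status anticipates by the end of September 2025.

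1. **Handling of missing data.** Show the baseline comparison by arm, next to the missing proportions by arm that are already planned, and label both as description. Remove the baseline comparison as the test of complete-case validity.
2. **Additional analyses.** When primary outcomes are missing and the complete-case analysis is kept, add an arm-specific delta (tipping-point) analysis. Vary the assumed admission risk of missing infants separately in each arm, and report the values at which the posterior probability of superiority crosses 99%.

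The second change addresses directly what the baseline comparison cannot: how different the missing infants would have to be, and in which arm, for the conclusion to change. The cost is a wording change and one further analysis of data already collected, with a little more reporting.

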## Statistical analysis plan

### Statistical principals

Outcomes will be collected with a standardised survey issued to parents/caregivers either over email or by telephone 7 and 21 days after enrollment in the BIPED study. Non-responders will be sent a second email and, if necessary, up to six attempted phone calls over 3 days. Once 21 days have elapsed following enrolment, the participant’s medical record will be reviewed to track any return ED visits, hospital admissions and additional healthcare contact. Admissions and ED visits reported by caregivers to study hospitals must be confirmed on medical record review. Similarly, at the six study hospitals where admissions and ED visits to non-study hospitals can be confirmed by administrative database review, non-study hospital ED visits and admissions reported on the survey will be confirmed. For study sites where visits and admissions to non-study hospitals cannot be confirmed by administrative database review, the caregiver’s report of and reason for these visits/admissions will be used to determine whether the participant met the study definition of admission. The final trial analysis will take place after every participant has reached 21 days after enrolment and all the data have been collected and cleaned. The analysis will be performed in a blinded manner.

The final trial analysis will use a Bayesian inferential framework based on the posterior probability that the EpiDex combination is superior to placebo for the primary and secondary outcomes. It will follow the intention-to-treat principle. The EpiDex combination will be declared superior to placebo if the posterior probability of superiority is above 99%, with simulations confirming a type 1 error rate of 4.1% with a probability of hospitalisation equal to 0.35 and a power of 81% with a target difference of 8%. Due to the likelihood principle, corrections for multiple comparisons will not be used. All estimates for the treatment effect will be reported using 95% high density posterior credible intervals, calculated using R [18] interfacing with Bayesian software such as JAGS, stan or INLA [19–21].

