### Analysis populations

The primary analysis will include all randomised participants for whom outcome data are available and who do not withdraw consent for the use of their data as an intention-to-treat analysis. A per protocol analysis that includes only eligible participants for whom we have outcome data, who do not withdraw consent for the use of their data, who complete all their ED-based medications and receive the correct dose (within ± 5%) and timing of medications will also be performed. Finally, we will examine our outcomes in the per protocol population while also excluding participants who did not take their second dose of oral medication (unless admitted to hospital within the 40-h second dose of oral medication window).

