### Analysis for the primary endpoint

We will compute the posterior probability that EpiDex results in a lower probability of hospitalisation than placebo using hierarchical Bayesian relative risk regression, adjusted for site. The prior for the treatment effect is from our expert elicitation exercise [17]. We will report the mean and 95% high-density posterior credible interval for the absolute risk difference and relative risk across the two treatment groups. A secondary analysis of the primary outcome will include only those participants who present with their first episode of bronchiolitis. All models will include minimally informative priors for the variance parameters [24] and other coefficients [25].

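### If primary outcomes are missing and complete-case analysis is rejected, the plan as written gives no inference for the primary question, and no sensitivity analysis covers missing outcomes

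*SAP article*

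**What the plan says.** All references are to the SAP article.

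- *Handling of missing data*. Below 5% missing, a complete-case analysis is done. Above 5%, the baseline characteristics of participants with and without missing data are compared, and the validity of a complete-case analysis is judged from that. A joint Bayesian model is offered when covariates are missing. For outcomes the rule differs: "In general, we will not jointly model or impute missing outcomes", and "If outcomes are missing and a complete case analysis is not used, then we will report descriptive statistics for this outcome", together with the reasons for loss. No outcome is exempted.
- *Analysis populations*. The primary analysis takes "all randomised participants for whom outcome data are available" and who have not withdrawn consent for use of their data.
- *Analysis for the primary endpoint*. The posterior probability that EpiDex lowers hospitalisation is to be computed "using hierarchical Bayesian relative risk regression, adjusted for site", with an elicited prior for the treatment effect. No condition is attached.
- *Statistical principals*. EpiDex will be "declared superior to placebo if the posterior probability of superiority is above 99" per cent.
- *Additional analyses*. The only missing-data sensitivity analysis is a complete-case analysis, run only if the analyses were adjusted for missingness.
- *Sample size calculation*. "We allowed for a 5% loss to follow up, leading to a total target recruitment of 864 participants, 432 per arm".

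**The concern.** The plan has three routes for missing data, and none yields an inferential result for a missing primary outcome once complete-case analysis is set aside. The covariate model cannot help the primary analysis, whose only stated adjustment is for site, which is known from randomisation. The sensitivity analysis cannot help either: it depends on an adjustment that is in general not made for outcomes, and it is itself complete-case. The trial could therefore reach analysis with a decision rule and nothing to apply it to, or settle the matter after the extent of missingness has been seen.

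The complete-case route is not neutral. Under *Primary outcome*, an infant admitted at the enrolment visit, or kept 12 h or longer, has already met the endpoint. Later loss to follow-up can remove only infants who were sent home, so having an observed outcome depends partly on the outcome itself.

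**Working it through.** **Step 1: the plan's own figure.** Inputs are "the sample size of 410 participants per arm for the BIPED study was selected", 5% loss, and allocation "by randomising participants in a 1:1 ratio". 410 / 0.95 = 431.6, rounded up to 432 per arm; 2 × 432 = 864. This reproduces. The 4.1% type 1 error and 81% power come from simulations with a prior that is not shown; they were not reproduced, and nothing below depends on them.

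**Step 2: how easily the 5% line is crossed.** 5% of 864 is 43.2, so 44 or more missing outcomes exceed it. With a binomial count (independent losses assumed), the probability of 44 or more is:

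| True loss | P(more than 5% missing) |
|---|---|
| 4% | 6% |
| 5% (as planned) | 47% |
| 6% | 89% |

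This treats loss to follow-up as a missing primary outcome. Record review should recover some of these.

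**Step 3: what follows above the line.** If complete-case analysis is judged valid, the primary model runs. If not, *Handling of missing data* gives descriptive statistics only. *Analysis for the primary endpoint* and *Statistical principals* require a posterior probability and a decision. The two cannot both be followed.

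**Step 4: complete-case bias.** Let i be the proportion admitted at enrolment, l the proportion admitted later within 7 days, and m the proportion of discharged infants lost, unrelated to later admission. The complete-case risk is

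(i + l(1 − m)) / (1 − (1 − i)m).

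The SAP gives no split between i and l. Assume i = 0.25 and l = 0.10 in both arms, so the true risk is 35% and the true difference is zero.

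- m = 0.15: (0.25 + 0.085) / (1 − 0.1125) = 0.335 / 0.8875 = 37.7%
- m = 0.05: (0.25 + 0.095) / (1 − 0.0375) = 0.345 / 0.9625 = 35.8%
- m = 0.10: (0.25 + 0.09) / (1 − 0.075) = 0.34 / 0.925 = 36.8%

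Losing 15% of discharged infants on placebo and 5% on EpiDex gives a false difference of 35.8 − 37.7 = −1.9 points; swapping the arms reverses the sign. Equal 10% loss raises both arms to 36.8% and leaves the difference at zero.

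With i = 0.28 and l = 0.07 (80% of admissions at enrolment), loss of 3% versus 10% gives 1.4 points, and 5% versus 15% gives 2.1 points.

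**Step 5: a true 8-point effect with the same loss proportion among discharged infants in both arms.** Assume 35% versus 27%, with 80% of admissions at enrolment.

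| Missing overall | Placebo | EpiDex | Difference | Risk ratio |
|---|---|---|---|---|
| None | 35.0% | 27.0% | 8.0 | 0.771 |
| 5% | 36.3% | 28.1% | 8.2 | 0.775 |
| 10% | 37.7% | 29.3% | 8.3 | 0.779 |

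Varying the enrolment share from 60% to 100% gives a difference of 8.1 to 8.2 points at 5% missing and 8.2 to 8.5 at 10%.

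**Step 6: what modelling recovers.** If outcomes are missing at random among discharged infants, the risk is i + (1 − i) × l/(1 − i). In the step 4 case this is 0.25 + 0.75 × (0.10/0.75) = 35% in each arm, whatever m is.

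**The case against.** The strongest reply is that the no-inference branch may never be reached. It needs more than 5% of primary outcomes missing, complete-case analysis then judged invalid, and no use of the exception that the words *in general* leave open. *Statistical principals* plans a second email, up to six calls, record review for every participant and, at six hospitals, database confirmation of admissions elsewhere. The missing-data section covers all outcomes, and survey-based ones such as symptom resolution and family expenses are more exposed than admission. This stands and lowers the severity. It does not supply a fallback: the exception is unspecified, and at sites without database confirmation admissions elsewhere rest on caregiver report.

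The bias illustration uses a threefold imbalance in loss. Of 432 per arm that is 432 × 0.75 × 0.15 ≈ 49 infants against 432 × 0.75 × 0.05 ≈ 16, which is a lot for a double-blind trial. That also stands; step 5 shows the effect is small when loss is equal.

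A reader might go further in two ways that the documents do not support.

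- One might infer that, with so many baseline items listed, chance differences would almost always defeat the complete-case check. The SAP sets no significance test and no rule that one differing item is decisive; it describes a judgement.
- One might infer that baseline differences prove missingness to be at random, and so repairable. They show only an association with observed variables and are compatible with loss that also depends on the unseen outcome.

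Offering a model for missing covariates is not a defect either: the subgroup and heterogeneity analyses may need it.

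**Conclusion.** The point holds in a conditional form. The SAP states a rule under which the primary outcome could receive descriptive statistics only, contrary to its own unconditional promise of a posterior probability and a decision. No planned sensitivity analysis addresses missing outcomes. The trigger sits at the planned loss rate, but crossing it does not by itself end inference, and the documents do not support saying that the trial will lose its primary result.

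The complete-case weakness is real but secondary. It raises the risk in both arms by about 1 point at 5% missing and 2 to 3 points at 10% (step 5 assumptions). It shifts the contrast by about 0.2 to 0.3 points when loss is equal, and creates a false difference of about 1.4 to 2.1 points under the unequal losses illustrated, against a target of 8. These sizes rest on assumed splits between enrolment and later admission and on loss unrelated to later admission among discharged infants. They concern loss to follow-up; withdrawal of consent for data use is a separate exclusion and could also remove admitted infants.

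This should be corrected before data lock, but it ranks below a defect that makes the plan unusable.

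**What to change.** Change *Handling of missing data* and *Additional analyses* for the primary outcome as follows.

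1. Delete the descriptive-only fallback. State that the posterior probability and credible interval from *Analysis for the primary endpoint*, with the elicited prior and site adjustment, will always be reported.
2. When outcomes are missing, treat them as unknowns under missing-at-random within infants discharged at the enrolment visit. Use enrolment-visit disposition, arm, site and collected baseline variables, for example through Bayesian multiple imputation feeding the unchanged primary model. Report complete-case analysis as a sensitivity analysis.
3. Add a delta-adjusted (tipping-point) analysis whatever the percentage missing, because missing-at-random cannot be verified from the data.

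The primary model itself should stay. Splitting it into enrolment and post-discharge parts would leave open how the elicited prior maps onto two treatment effects, and the stated 4.1% type 1 error and 81% power would need checking again.

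The cost is revised wording and modest extra programming before data lock, which *Trial status* expects by the end of September 2025. No new data are needed.
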